**Qualitative Measures**

We aim to undertake qualitative interviews with participants and with staff who refer service users/patients to the study. We anticipate this will help us capture any emerging changes in implementation, including potential facilitators and barriers to implementation. The Interview topic guide is included as part of the HRA documents submission and includes questions regarding the trial, including the acceptability and preferences around questionnaires being used (if these are “too many” or acceptable). The Participants Interview schedule has been developed based on a theoretical framework of acceptability (Sekhon et al. 2017) covering areas such as affective attitude, burden, ethicality, intervention coherence, opportunity costs, perceived effectiveness and self efficacy) with questions framed in straightforward language.

We also seek to interview therapists who have delivered an imagery focused therapy for psychosis, to help inform understanding of the delivery of the therapy and to help make refinements to the therapy manual.

**Inter-Rater Reliability Measures**

All assessment sessions will be recorded with informed written consent. This to ensure there is sufficient inter-rater reliability across the assistants when administering the PANSS and PSYRATS interview measures, as part of an integrated interview protocol.

**Details of therapy sessions Fidelity & iMAPS Fidelity Scale Development**

Therapy sessions are to be audio/video recorded. A number of these will be reviewed in supervision every few weeks to be rated against the CTS-R and/or the CTS-PSY (Haddock et al. 2001) in clinical supervision. We will also seek to develop an adapted imagery focused therapy fidelity rating scale, with elements specific to the iMAPS protocol. The aim of this nested study will be to develop an iMAPS therapy fidelity scale, investigate it’s psychometric properties and examine it’s utility in evaluating the adherence of therapists engaged in this type of therapy with people experiencing psychosis. Please see appendix 4 for brief outline of aims, methods and planned analysis.

We will identify an experienced therapist colleague outside of the trial team to be added as part of the study team (letter of access if needed, etc) and to rate a random selection of sessions for fidelity.

**Health Economic Analysis**

Descriptive statistics will be used to summarise the range of service use and costs and the range of health benefits. Costs and baseline data will be described to explore key service use/cost drivers. A similar approach will be used to explore the range of health benefits and how well the generic EQ-5D-5L correlates with other outcome measures in this participant group.

Data will be collected on the utilisation of primary, community and secondary care, including medications, admissions, A&E attendances and bed-days.

### Number of Assessments and Measures (Participant Burden)

The trial has been designed to minimise the number of interviews and self-report questionnaires. Recent clinical trials conducted in the UK involving people with psychosis have had a significantly greater number of assessments. For example, the [Youth Mental Health and Resilience Study](https://doi.org/10.1186/s12888-017-1206-5) had >24 assessments per assessment point, including 10 interviews or psychometric assessments and 3 brain imaging assessments); the NIHR [FOCUS Trial](https://dx.doi.org/10.1186%2Fs12888-016-0983-6) had > 26 assessments per timepoint including 8 interviews or assessments)

Our trial has minimised the number of assessment points and we have carefully chosen our measures to gather essential information. Previous clinical trials we have been involved with have included longer research assessment durations. This experience has demonstrated that with regular breaks and the offer of completing the assessment over two or more appointments, people with psychosis have found the assessment process acceptable. Participants will each receive £15 per assessment (£45) in total to reimburse them for their time and any travel. If they take part in the qualitative interview, they will receive an additional £15. Staff who take part in the referrrer’s interview will also receive £15 as an honorarium (assuming they take part in non-working time e.g. beginning or end of working day).

We estimate the informed consent process will take approximately 15-20 minutes. We will then undertake a screening assessment to confirm eligibility (see earlier section 3.4 Recruitment). This will be discussed by the RA with the PI and the outcome fedback to the potential participant. The initial baseline assessment will take approximately 2 hours. Participants will be invited to complete this over two or three meetings, with a mixture of face to face and/or online video assessment as part of the offer. Breaks will be offered on request and/or every 30 mins.

The end of therapy assessment and follow up assessment will begin with confirming continued informed consent, and then completion of the measures. There will be the same offer to complete over two or more meetings and breaks will be frequently offered.

## FOLLOW UP ASSESSMENTS

Participants who are randomised will be invited to complete a follow up assessment at 16 weeks (end of therapy assessment) and again at 28 weeks (follow up assessment).

## Withdrawal

Withdrawal from the study will occur if:

- The participant decides to withdraw from the trial for any or no-stated reason

## Lost to Follow Up

Participants who unable to be contacted at 16 week follow up will be contacted again at 28 week follow up, unless they have withdrawn (or been withdrawn for clinical reasons) from the trial. Those who we are unable to contact at 28 weeks follow up will be lost to followup.

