### Participant withdrawal

Participants in the study are free to withdraw from participating at any point, without giving a reason and without their legal rights or usual care being impacted. It is possible for a participant to with draw from receiving the therapy, but continue to remain in the trial for the follow up assessments, in essence, participants will be asked if they are willing to continue data collection assessments at 16 weeks and 28 weeks, if they wish to withdraw from the iMAPS intervention. While being reminded of their right to withdraw without giving a reason, we will politely ask if they are willing to give a reason, but remind them that this is entirely voluntary.

If continued participation for some reason is assessed by the researchers to be harmful in some way, then we may withdraw a participant. The Trial Steering Committee (TSC) which incorporates a Data Monitoring and Ethics function will review all instances of adverse events, regardless of whether they are judged to be attributable to the trial or interventions. Reviewing this information, the independent committee members will decide if a participant should be withdrawn from the study. All adverse events deemed related to study participation will be reported the Research Ethics Committee (See Section 9 for further details).

There is a possibility that individuals taking part may lose capacity to consent to continue participating in the study. In this event, we would pause their participation to see if they regain their capacity (acknowledging that capacity fluctuates in people with psychosis and may be temporary). However, if they continue to lack capacity, this may also mean they are no longer able to consent to ongoing participation in the study or for their data to be retained. In line with previous studies (including the iMAPS case series) we will seek informed consent in advance from all participants to retain their data if they subsequently withdraw because of loss of contact or are withdrawn by the study team due to loss of capacity

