|  | AEP | 5 |  | End of therapy or at dropout, if consent to send has been given in advance. |  |

Note: PANSS: Positive and Negative Syndrome Scale (Kay et al., 1987); PSYRATS: Psychotic Symptom Rating Scales(Haddock et al., 1999); QPR: Questionnaire about the Process of Recovery(Law et al., 2014); MIPQ: Mental Imagery in Psychosis Questionnaire/Visual Analogue Scales (Taylor et al., 2019); PIQ: Psychosis Imagery Questionnaire Taylor et al. 2022); BCSS, Brief Core Schema Scale (Fowler, Freeman, Smith, Kuipers, Bebbington, & Bashforth, 2006); TALE: Trauma and Life Events Checklist (Carr et al., 2018); ITQ: International Trauma Questionnaire (Cloitre et al., 2018); BES: Basic Emotions Scale (Power, 2006); BAI: Beck Anxiety Inventory (Beck et al., 1988); CDS: Calgary Depression Scale (Addington et al., 1993); WEMWBS: Warwick Edinburgh Mental Well Being Scale (Tennant et al., 2007); PSP: The Personal and Social Performance Scale (Morosini et al., 2000); EQ-5D-5L: The EuroQol 5-Dimenson 5 Level measure (Janssen et al., 2013); REQol-10: Recovering Quality of Life Measure (Keetharuth et al., 2018); Economic Patient Questionnaire (Shields et al., 2020); WAI-SR-client: Working Alliance Inventory – client version (Hatcher & Gillaspy, 2006); WAI-SRT-therapist: Working Alliance Inventory – therapist version(Hatcher & Gillaspy, 2006); CTS-R: Cognitive Therapy Rating Scale – Revised (Blackburn et al., 2001); Cognitive Therapy Scale for Psychosis (Haddock et al., 2001); Clinical Global Impression- Improvement Participant Version (CGI-IP) Clinical Global Impression - Severity Participant (CGI-SP) Version; Adverse Effects of Psychotherapy Questionnaire (Hutton, 2013)

We will also capture postcode and calculate the Index of Multiple Deprivation Decile by using the following website link:

<http://imd-by-postcode.opendatacommunities.org/imd/2019>

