**Usual Care**

Usual care will involve interventions offered by an early intervention service or a community mental health team (fortnightly/monthly visits from social worker, mental health nurse, outpatient psychiatry reviews quarterly, medication, routine CBT). The study would not seek to restrict access in routine care to CBT. We will record during the trial by asking participants and by reviewing their clinical record and record any service users in the usual care arm of the trial who receive routine CBT or other psychological intervention. However, we know there are still significant barriers to NHS therapy. The 2020 English NCAP Psychosis National Audit collected data on access to CBT, defining a course of CBT as receiving just one session of therapy, (rather than the min. 16 sessions recommended by NICE). Even with this low threshold, only 49% of service users had this offer in EI. Secondary care services have historically had even poorer commissioner investment.

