## ADVERSE EVENTS

***Definitions***

| **Term** | **Definition** |
| --- | --- |
| **Adverse Event (AE)** | Any untoward medical occurrence in a participant to whom psychological therapy/assessment or qualitative interview has been administered.  Non severe adverse events will be defined as a score of >3 (Agree quite a lot or a lot) on any item of the participant rated 26 item Adverse Events of Psychotherapy Questionnaire (AEP; Hutton, 2016; Pyle et al 2016) which is given to participants on either completion of therapy, or if they have given informed consent, sent to those who drop out or end therapy early. |
| **Adverse Reaction (AR)** | An untoward and unintended response in a participant to a psychological therapy/assessment or qualitative interview which is related to the therapy/assessment or interview administered to that participant.  The phrase "response to a psychological therapy/assessment or qualitative interview" means that a causal relationship between a trial therapy/assessment or interview and an AE is at least a reasonable possibility, i.e. the relationship cannot be ruled out.  All cases judged by either the reporting clinically qualified professional or the Chief Investigator (acting on behalf of the Sponsor) as having a reasonable suspected causal relationship to the psychological therapy/assessment or qualitative interview qualify as adverse reactions. |

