Our iMAgery focused therapy for Psychosis approach has previously been tested in a case series and no severe adverse events were reported. Building on work by others in psychological treatments for psychosis, we wish to carefully record and report adverse events of psychological interventions and wish to implement a protocol developed assessing and managing any such risk, which will be completed at end of treatment and at follow up by research assistants who are blind to the allocated group. We are adding the use of the CGI and additional criteria below.

This protocol will also be completed by clinicians during the intervention, that is each session, to complete an assessment of severe adverse events, for clinical purposes.

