**SAEs**

All SAEs **related** to the psychological therapy/assessment or qualitative interview occurring between baseline until end of study must be recorded on the SAE report form and emailed to Sponsor immediately and within 24 hours of the research staff becoming aware of the event. Refer to the SAE form for the information that will be collected for all SAEs.

Any change of condition or other follow-up information should be emailed to the Sponsor as soon as it is available or at least within 24 hours of the information becoming available. Events will be followed up until the event has resolved or a final outcome has been reached.

| **Email completed all SAEs FAO:**  [**[contact]**](mailto:[contact])  [**[contact]**](mailto:[contact]) |
| --- |

SAEs must be followed-up until resolution and sites must provide follow-up SAE reports if the SAE had not resolved at the time the initial report was submitted.

On receipt of the SAE Report Form, the Sponsor will send an acknowledgement of the SAE. This acknowledgement will include an SAE reference number which should be included on all future correspondence regarding the SAE.

The SAE Report Form will be reviewed by the CI for assessment of causality. If the SAE is related to the psychological therapy/assessment or qualitative interview, the CI will review the expectedness in relation to the nature or severity of an event which is not consistent with the effects or consequences of a psychological intervention. In the case that the SAE is related and **unexpected**, the study team will submit a report to REC, HRA and the Sponsor within the expedited timeframes.

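### Suicidal crisis is scheduled for rating only at weeks 16 and 28 but reported over all randomised, so its proportion can be understated; people withdrawn for clinical reasons also lose their remaining assessment

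*Combined protocol and SAP*

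**What the plan says.** **Denominator.** SHEAP 5.3 takes everyone randomised as the safety population. SHEAP 7.6 plans, by arm, the number and proportion of participants with a safety event, a breakdown by category, and differences in event rates with 95% CIs. It gives no other denominator and no rule for people who were not assessed.

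**Event definition.** Protocol 3.17 and SHEAP 7.6 define suicidal crisis without attempt as a rating of 2 on CDSS item 8. The assessment table in Protocol 3.11 places that scale at baseline, 16 weeks and 28 weeks. Severe symptom increase rests on the CGI, whose participant forms the same table lists at each therapy session.

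**Other capture.** Protocol 3.17 describes a safety assessment "which will be completed at end of treatment and at follow up by research assistants who are blind to the allocated group"; clinicians also complete it at each session, for clinical purposes. Under Protocol 3.18, related SAEs "occurring between baseline until end of study must be recorded on the SAE report form", with notification "within 24 hours of the research staff becoming aware of the event". The adverse effects of psychotherapy questionnaire (AEP) is given "End of therapy or at dropout, if consent to send has been given in advance", and SHEAP 7.6 tabulates it for the intervention arm only. The Usual Care text in Protocol 3.16 mentions "reviewing their clinical record and record any service users in the usual care arm of the trial who receive routine CBT"; no safety use of the record is named.

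**Withdrawal.** Protocol 3.6.1 says "If continued participation for some reason is assessed by the researchers to be harmful in some way, then we may withdraw a participant", and lets the steering committee decide on withdrawal too. The same section keeps the 16- and 28-week assessments open to people who choose to leave therapy. Protocol 3.14 has people missed at week 16 tried again at week 28, "unless they have withdrawn (or been withdrawn for clinical reasons) from the trial".

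**Missingness.** SHEAP 6.4 and 7.4 tabulate withdrawals and losses by arm, with reasons.

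**The concern.** A proportion over all randomised treats everyone without a recorded event as event-free. That is reasonable where an event would come to light without a visit. It is less so where the event is itself a scale rating. A person with neither a 16- nor a 28-week CDSS adds one to the denominator and, outside incidental capture, nothing to the numerator.

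Two things could make this matter beyond simple dilution. Incidental capture is not the same in the two arms: iMAPS participants are checked at sessions and may receive the AEP, and TAU participants have neither. And people withdrawn for clinical reasons are plausibly at higher risk than those who stay, yet the plan ends contact with them. At stake is how far a reader can trust the harms table, in particular a low crisis proportion or an arm difference.

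**Working it through.** **Inputs from the documents**

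- 45 randomised, at least 36 with outcome data (Protocol 3.21, SHEAP 4.4). Check of the plan's own precision figure: 36/45 = 80%, exact 95% CI 65.4% to 90.4%, width 25.0 points, as stated.
- Amber/red retention boundary: 60% (Protocol 3.11).
- Supplementary Table 4a column totals (iMAPS, TAU): 31 and 14 at baseline; 25 and 11 (36) at week 16; 18 and 8 (26) at week 28.

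**Inputs not in the documents (assumed):** event risks; the share *c* of unseen participants' events that is still captured (0 to 1, with 0 an extreme bound); the relative risk *m* in unseen against seen participants.

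**1. Dilution with equal risk.** With *r* the share seen, recorded/true = r + (1 − r)c.

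| r | c = 0 | c = 0.5 | c = 1 |
|---|---|---|---|
| 36/45 = 0.80 | 0.80 | 0.90 | 1.00 |
| 0.60 | 0.60 | 0.80 | 1.00 |
| 26/45 = 0.578 | 0.58 | 0.79 | 1.00 |

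The last row applies only to events after the week-16 visit, because people seen at week 16 were observed to that point.

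**2. Higher risk in the unseen.** With c = 0, recorded/true = r / [r + (1 − r)m]. At r = 0.80, m = 2 gives 0.8/1.2 = 0.67 and m = 3 gives 0.8/1.4 = 0.57. These are bounds, since some capture exists.

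**3. Arm difference.** Retention in the supplement is balanced: 25/31 = 81% and 11/14 = 79% at week 16; 18/31 = 58% and 8/14 = 57% at week 28. With a true 20% in both arms and c = 0, week-16 retention alone gives 0.20 × 25/31 = 16.1% and 0.20 × 11/14 = 15.7%, a difference of 0.4 points. Unequal capture can do more. At r = 0.80 in both arms:

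- true 20% v 20%: full capture in iMAPS and none in TAU gives 20 − 16 = +4 points; the reverse gives −4;
- true 20% v 10%: the recorded difference runs from 16 − 10 = 6 to 20 − 8 = 12 points.

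The direction is therefore not fixed.

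**4. Worked example.** Assume 4 crisis cases among 36 people rated at least once.

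- Over all randomised: 4/45 = 8.9% (exact 95% CI 2.5 to 21.2).
- Among those rated: 4/36 = 11.1% (3.1 to 26.1).
- Shift: 2.2 points.

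A denominator requiring both visits would do worse. If 2 of the 4 cases were rated at week 16 and then lost, and 26 people had both ratings, it gives 2/26 = 7.7% (0.9 to 25.1). At least one rating is the better rule.

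**5. Can a reader rebuild the denominator?** Not from the planned tables.

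- The loss tables count withdrawals and losses, not ratings.
- The completion outputs under Objective 3 in SHEAP 7.2 cover PANSS, PSYRATS, QPR, MIPQ and BCSS, not the CDSS.
- A valid CDSS total does not prove that item 8 was rated, because SHEAP 7.1 allows 3 of the 9 items to be imputed.
- Being counted at a visit is not the same as being rated: Supplementary Table 5 has PANSS response missing for 2 of 36 at week 16 and 2 + 3 = 5 of 26 at week 28.

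**The case against.** The strongest answer is that the plan already covers most of this. Reporting follows the CONSORT pilot extension (Protocol 3.22, SHEAP 7), whose checklist asks for the denominator of each analysis, and losses are tabulated by arm with reasons. Research assistants are embedded in the clinical teams (Protocol 3.5), and participants are under an NHS team with a keyworker or duty worker. Supplementary Table 6 lists 13 unrelated events (2 SAEs and 11 AEs), so recording went beyond related events. Retention is balanced, and the worked shift is small.

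Much of that stands. It makes zero capture remote and keeps the point minor. But the general CONSORT commitment does not change the all-randomised rule in SHEAP 5.3, and neither the loss tables nor the event listing shows how many people were rated on item 8.

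Four stronger readings are tempting, and the documents do not support them.

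- *An unrated participant can never be recorded as a case.* Clinicians check iMAPS participants at each session, and staff may hear of a crisis.
- *Safety follow-up is cut short at final loss.* Loss is declared only after failed contact at week 28, the last planned visit. The gap is the time since last contact.
- *A definitive trial will take its event rates from these figures.* No section says so; sample-size planning in SHEAP 7.2 uses outcome SDs.
- *The bias favours iMAPS.* Step 3 shows that it can go either way.

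A fair criticism of the remedy also stands: a denominator of people rated at least once still counts someone seen only at week 16 as event-free to week 28. For the CGI, which is scheduled at therapy sessions, such a rule would mix unequal exposure between arms.

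**Conclusion.** The point holds as a minor one. As written, the plan reports suicidal crisis over all randomised although its defining rating is scheduled after baseline at only two visits, so the proportion can be understated and capture can differ by arm. The size is unknown. At 80% retention and equal risk the recorded proportion lies between 0.80 and 1.00 of the true one, depending on a capture share that the documents do not give. The illustrative 2.2-point shift sits well inside intervals some 19 to 23 points wide. Progression rests on recruitment, retention and adherence, so no progression decision turns on it.

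The withdrawal wording is a separate, smaller gap. Protocol 3.6.1 keeps assessments on offer to people who choose to leave therapy. No equivalent is stated for those withdrawn by the researchers or the committee, and 3.14 excludes people withdrawn for clinical reasons from re-contact. How many people this affects is not given.

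The SAE form, monitoring plan and data management plan are not in the text available, and could describe a further capture route.

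**What to change.** **(a) SHEAP 7.6.** Keep the proportion over all randomised. For the CDSS-rated category, print by arm the number rated on item 8 at week 16, at week 28, and at least once after baseline. Repeat the proportion and the arm difference among those rated at least once, with a note that people seen only at week 16 are observed only to that point. A case rated at week 16 and later lost then stays in both numerator and denominator. For CGI-rated events, report the number rated by arm and by source (therapy session or research visit), and do not treat the arms as equally observed.

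**(b) Protocol 3.6.1 and 3.14.** Make a withdrawal started by the researchers or the steering committee a stop of the intervention only. Keep offering the 16- and 28-week assessments unless the participant declines, lacks capacity, or the assessments themselves are the concern.

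**Cost.** (a) adds a few counts and one repeated proportion and difference. (b) is two wording changes. The downside is a little analysis and assessor time, and possibly less favourable event figures.
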